# Evaluation of implementation and effectiveness of digital adherence technology with differentiated care to support tuberculosis treatment adherence and improve treatment outcomes in Ethiopia: a study protocol for a cluster randomised trial

**DOI:** 10.1186/s12879-021-06833-x

**Published:** 2021-11-10

**Keywords:** Tuberculosis, Smart pillbox, Medication label, Trial, Cluster randomised, Pragmatic, Ethiopia

## Abstract

**Background:**

Digital adherence technologies (DATs) are recommended to support patient-centred, differentiated care to improve tuberculosis (TB) treatment outcomes, but evidence that such technologies improve adherence is limited. We aim to implement and evaluate the effectiveness of smart pillboxes and medication labels linked to an adherence data platform, to create a differentiated care response to patient adherence and improve TB care among adult pulmonary TB participants. Our study is part of the Adherence Support Coalition to End TB (ASCENT) project in Ethiopia.

**Methods/Design:**

We will conduct a pragmatic three-arm cluster-randomised trial with 78 health facilities in two regions in Ethiopia. Facilities are randomised (1:1:1) to either of the two intervention arms or standard of care. Adults aged ≥ 18 years with drug-sensitive (DS) pulmonary TB are enrolled over 12 months and followed-up for 12 months after treatment initiation. Participants in facilities randomised to either of the two intervention arms are offered a DAT linked to the web-based ASCENT adherence platform for daily adherence monitoring and differentiated response to patient adherence for those who have missed doses. Participants at standard of care facilities receive routine care. For those that had bacteriologically confirmed TB at treatment initiation and can produce sputum without induction, sputum culture will be performed approximately 6 months after the end of treatment to measure disease recurrence. The primary endpoint is a composite unfavourable outcome measured over 12 months from TB treatment initiation defined as either poor end of treatment outcome (lost to follow-up, death, or treatment failure) or treatment recurrence measured 6 months after the scheduled end of treatment. This study will also evaluate the effectiveness, feasibility, and cost-effectiveness of DAT systems for DS-TB patients.

**Discussion:**

This trial will evaluate the impact and contextual factors of medication label and smart pillbox with a differentiated response to patient care, among adult pulmonary DS-TB participants in Ethiopia. If successful, this evaluation will generate valuable evidence via a shared evaluation framework for optimal use and scale-up.

*Trial registration*: Pan African Clinical Trials Registry PACTR202008776694999, https://pactr.samrc.ac.za/TrialDisplay.aspx?TrialID=12241, registered on August 11, 2020.

**Supplementary Information:**

The online version contains supplementary material available at 10.1186/s12879-021-06833-x.

## Background

Globally, an estimated 10.0 million people became ill with tuberculosis (TB) in 2019, with 7.1 million diagnosed, treatment success rate of 85%, and about 1.4 million deaths [1]. TB treatment is the core of TB control and prevention, but poor adherence to treatment can lead to disease relapse, drug-resistance, and forward TB transmission [2]. Poor treatment outcomes are disproportionately high in low-income countries and among low-socio-economic groups within countries [1]. The World Health Organization (WHO) End TB Strategy, in alignment with the Sustainable Development Goals (SDG), has set ambitious goals to end the global TB epidemic by 2035 [3]. This strategy requires high-impact interventions to ensure equitable access to high-quality diagnosis, treatment, care, and prevention, without imposing catastrophic costs, to people with TB.

The WHO-recommended Directly Observed Treatment (DOT) approach has been the most widely implemented strategy to support administration of TB treatment and ensure that patients successfully complete the treatment period. While significant improvements in TB treatment outcomes have been observed after the introduction of DOT, global treatment success rates for both drug-sensitive (DS)-TB and particularly drug-resistant (DR)-TB remain below the 90% target for 2025 set out in WHO’s End TB strategy [1, 3]. The implementation of facility-based DOT places a significant burden on both patient and health systems [4–7]. For patients, DOT is associated with stigma, loss of autonomy and lost income. For providers DOTS is resource intensive and a burden on busy health care facilities. Furthermore, the traditional DOT approach assumes that all TB patients require the same level of monitoring and support, rather than focusing care on patients that are at higher risk for non-adherence and poor outcomes, and therefore in need of intensified support [8].

Adherence to TB treatment is essential to attain durable cure and avoid the emergence of drug resistance [9]. It is also an important element of clinical trials of TB treatment as it strongly influences the treatment outcome and therefore evaluation of the intervention [10]. While there are variations across studies in classifying adherence, definitions of adherence to TB treatment have emphasized patients’ roles in medication-taking throughout the treatment course following the recommendations from the provider [2, 11]. Adherence to treatment has been shown to be influenced by patient characteristics, treatment regimen complexity, and the health care setting [2, 11], and the use of adherence interventions such as electronic medication monitors and mobile text messaging has shown to improve TB treatment outcomes [12–15]. Adherence technologies may be expected to vary in utility by patient characteristics as well as cultural and health care setting.

Currently, a number of digital adherence technologies (DATs), such as electronic medication monitors and text messaging, are available, offering approaches to improve treatment adherence [16]. These technologies are digital tools that utilize mobile phone, computer, web-based and/or electronic sensor technology to support patient care and adherence. These technologies often employ reminders to patients for taking treatment, as well as the capture of detailed, timely, patient-specific adherence data to be made available to the patient’s health-care provider for monitoring. Electronic medication boxes are medication monitoring devices (often with audio-visual reminders) that store TB medications and which record and transmit patient box access to give the provider the patients’ dosing history. The medication sleeve is also a type of electronic medication monitor that consists of medication blisters wrapped in special envelopes with printed codes. Patients use these codes when making a toll-free call/text to let their health care provider know when they have taken their medication [16]. Such digital innovations are beneficial because they may remind patients to take their medications. Digital adherence technologies may be employed with a web-based platform to compile dosing histories that allow health-care providers to review adherence daily. Although the End TB Strategy recommends using digital adherence technologies, evidence that such technologies improve adherence and treatment outcomes is still limited [17].

Recent randomised studies in countries in Africa and Asia documented mixed results regarding effectiveness of medication monitoring to reduce poor medication adherence and treatment outcomes [18–24]. However, it is not clear whether these findings can be generalised to real-life circumstances that are not reflected in randomised controlled trials. Furthermore, the patient and health-care provider acceptability and uptake of these tools have been shown to be vary across countries and settings [25–27]. Cultural or material circumstances may operate differently on the utility or acceptability of DATs to deliver the targeted treatment support that is needed to meet the End TB goals. Data from individual trials might not typically provide policy makers with all the information needed to replicate their success in real-life settings and specific contexts.

Ethiopia is among the 30 high TB and TB/ HIV burden countries, with annual estimated TB incidence of 157/100,000 populations and death rate of 19 per 100,000 populations for 2019 [1]. Since 1997, Ethiopia has adopted Directly observed treatment, short-course (DOTS) as its core treatment strategy, with the development of the first combined Tuberculosis and Leprosy Prevention and Control Program manual [28] and the national control program endorsed the global STOP TB and END TB strategies over subsequent years [28, 29]. However, non-adherence to TB treatment and poor treatment outcomes remain the major barriers to achieve the national END TB Strategy targets [30–32]. As TB remains a public health problem with significant burden among affected and at-risk populations in Ethiopia, the country’s national strategic plan recommends evidence-based and high-impact interventions that will keep the nation on track to end the TB epidemic [29]. The implementation of DATs has the potential to promote a cost-effective, patient-centred approach to improve TB treatment adherence across a range of settings and thereby reduce TB incidence and mortality to end TB as a public health problem. The Adherence Support Coalition to End TB (ASCENT) Consortium members [Koninklijke Nederlandse Centrale Vereniging (KNCV) Tuberculosis Foundation, The Aurum Institute, London School of Hygiene & Tropical Medicine, and Program for Appropriate Technology in Health (PATH)] in partnership with the governments of five countries (Ethiopia, Philippines, South Africa, Tanzania, and Ukraine) are implementing the ASCENT project, that will contribute evidence to support the adoption and uptake of DATs. In Ethiopia, this evidence will be generated through a pragmatic cluster randomized trial to implement and assess the effectiveness of medication labels and smart pill boxes linked to a web-based adherence platform, to create a differentiated care response to patient adherence and improve TB care among adult pulmonary DS-TB participants.

## Objectives

The primary objective of the trial is to evaluate whether implementation of daily adherence monitoring using either smart pill box or medication label, with differentiated response to patient adherence, decreases the proportion of adult pulmonary DS-TB participants with unfavourable outcomes (defined as poor end of treatment outcome or recurrence up to 6 months after the scheduled end of treatment) compared with the standard of care. The secondary objectives are to describe longitudinal DAT engagement and fidelity to adherence tools, project the epidemiological impact of scale-up of the interventions, estimate the cost-effectiveness and explore the feasibility and acceptability of implementing the interventions.

## Methods/Design

### Study design

This is a pragmatic three-arm cluster randomised trial (CRT) with the health facility as the unit of randomisation. A total of 78 health facilities from two regions are included in the trial. Health facilities were randomised (1:1:1), using stratification and restriction, to either the (i) smart pill box or (ii) medication label, both with daily monitoring and differentiated response to patient adherence, or (iii) standard of care.

### Study setting

Ethiopia is administratively divided into ten regional states and two chartered cities. The trial will be conducted in Addis Ababa city (the capital of Ethiopia) and Oromia region. These geographical settings were chosen in consultation with the National TB Programme (NTP) and the health facilities were selected in collaboration with NTP and the respective Regional Health Bureaus. The study health facilities include both large and small, urban, and rural facilities.

### Study population

All adult pulmonary DS-TB participants in the selected 78 health facilities who fulfil the following inclusion criteria will be invited to participate: aged 18 years or over, expecting to stay in the study area for at least 12 months, not requiring hospitalization, and providing consent. All who consented will be followed up for 6 months after treatment completion.

### Intervention

Participants in facilities randomised to either of the two intervention arms will be offered a smart pill box or medication label linked to the ASCENT web-based adherence platform for treatment adherence monitoring.

### Intervention arm 1: smart pill box

Participants in this arm will receive a smart pill box (evrimed 1000c), known also as Medication Event Reminder Monitor System (MERM). Dosing instruction and anti-TB drugs will be placed inside of the box. The box enables a configurable audio-visual reminder at a pre-defined time based on participants’ preference. When participants open the box, the embedded electronic device sends a signal in real-time to automatically log their daily dose to the ASCENT web-based application via a built-in mobile internet connection. If connectivity is temporarily unavailable, opening events are stored in the device memory and uploaded automatically when internet connectivity resumes. This allows the TB care provider to use the ASCENT adherence data platform to evaluate daily dosing and offer differentiated care (Table 1) as appropriate.

**Table 1 Tab1:** Differentiated care response to patient adherence in intervention arms

Trigger	Intervention
Dose recorded (daily)	Medication label: message confirmation from patient of recorded dose Smart pill box: box opening (sound and/or light)
Patient missed daily dose (1 day)	Same day: patient receives a reminder SMS at 3 pm* Next day: HCW will receive a notification of patients with a missed dose on their Task List Follow-up actions: phone call to patient or treatment supporter, unless HCW is aware of a network issue**
Missed daily dose (2 consecutive days)	Same day: patient receives a reminder SMS at 3 pm* Next day: HCW will receive a notification of patients with a missed dose ion their Task List Follow-up actions: phone call to patient or treatment supporter**, unless HCW is aware of a network issue***
Patient persistently missed doses (≥ 5 consecutive doses or multiple times)***	Escalation to community health worker for home visit using a standardised set of messages and counselling
Patient persistently missed doses (> 14 consecutive doses or multiple times missing 7 doses)	Discontinuation from DAT intervention and switch to daily DOT under the HCWs observation for TB patients with persistent non-adherence will be considered

*SMS* short message service; *HCW* health care worker

*Among patients with a mobile phone; **If daily DOT resumes as the standard of care, phone calls will be replaced with escalation to community health worker for home visit; *** among patients with mobile phone access (either their own or treatment supporter)

### Intervention arm 2: medication labels

Participants in this arm will have a label, containing a code unique to a 1-week period, placed on their fixed-dose blister-packaged TB medication. When their daily dose is taken, participants will message this code using a toll-free text, which automatically logs their daily dose to the ASCENT web-based application. With the adherence data collected to the platform, the same procedure is used as for intervention arm 1 for offering differentiated care (Table 1), as appropriate. Participants who do not have access to a mobile phone will be given a smart pill box.

Originally the medication sleeve approach as used in the Uganda stepped-wedge trial [19] was planned, but due to frequent changes in the dimensions of the packaging used for TB medication which was also difficult to forecast, the label approach was adopted instead.

### Standard of care

Participants in the control arm, will utilize the standard of care for TB treatment support in the facilities randomized to this arm. During the intensive phase of treatment, this entails direct observation of medication intake by a health worker or TB treatment supporter, at a health facility (hospital, health center or health post), at patient’s workplace, residence institution or home. During the continuation phase, medication intake is under direct observation by a TB treatment supporter or through self-administration upon consultation with the TB provider. Missed clinic appointments should result in a phone call to the patient and missing two consecutive clinic appointments should prompt a home visit by a health care worker (HCW).

### Differentiated care delivery based on adherence to treatment

Participants in the intervention arms will have their daily adherence data from their DAT recorded on the ASCENT adherence platform.

TB care providers can remotely access and review their participants adherence data through the ASCENT adherence platform mobile Android app. Through this app, the TB care providers can see the day of treatment and medication taking history for patients on treatment for TB at their facility. It has built in data analytics to easily visualize and identify which participants have not taken their daily dose on a patient level dosing calendar. TB care providers offer interventions according to the number of doses a patient has missed. Table 1 summarizes the activities related to differentiated care response.

### Randomization

Stratified, restricted randomisation of health facilities was used to ensure reasonable baseline balance between the intervention arms and standard of care arm [33]. Stratification was on region and treatment outcomes in 2017–2019 (from the NTP TB registers), which divided the study facilities into four groups. The restrictions further considered data from all study facilities’ NTP TB registers and included percentage with poor treatment outcome; number of DS-TB registrations; HIV prevalence among DS-TB and urban/rural facility.

### Trial outcomes

The primary endpoint is a composite unfavourable outcome, similar to previous TB treatment trials [34–36] and the DAT intervention being evaluated in China [37], defined as either a (i) poor end of treatment outcome (lost to follow-up, death or treatment failure or (ii) treatment recurrence measured 6 months after the scheduled end of treatment). The secondary outcomes are:

Among adult pulmonary DS-TB participants in all arms:(i)Poor end of treatment outcome (defined as above).(ii)Lost to follow-up during treatment.

Among adult pulmonary DS-TB participants in intervention arms(i)Longitudinal technology engagement with the DAT.(ii)Fidelity to the DAT (includes the number of messages sent to participants and HCWs, number and length of phone calls to and from participants, number of health facility visits by participants and number of home visits to participants as well as describing device failures, inability to engage with the technology and cell phone access).

TB patients enrolled in the trial TB care providers and key stakeholders will also be interviewed to explore the institutional feasibility and acceptability of implementing the DAT.

### Impact modelling

The trial results will be used to inform a *Mycobacterium tuberculosis* transmission model for Ethiopia, which will be used to project the expected long-term epidemiological impact if the interventions were to be scaled up across the country. This model will include treatment pathways to calibrate DS-TB incidence and mortality in Ethiopia, including a detailed description of the treatment pathway and implementation of DAT. The model outcomes will include the impact of the interventions on TB deaths and cases averted, as well as TB patient costs averted through a potential reduction in clinic visits required.

### Economic evaluation

The effectiveness, utilisation, and cost data collected during the trial will be used to estimate the cost-effectiveness of the (i) smart pill box with differentiated care and (ii) medication label with differentiated care when compared against the standard of care for DS-TB patients in Ethiopia. A societal perspective will be taken in the analysis, estimating the cost to the provider of providing the service plus the costs incurred by patients in using the service. Provider costs will include the above service-level costs, specifically the costs of training and supporting the implementation of the intervention. Since TB disproportionately affects patients of lower socio-economic status, TB prevention through effective treatment adherence may change how TB is distributed across socioeconomic strata in a population. Using the results of the trial differentiated by socioeconomic status, we will quantify trade-offs related to health inequality in the decision to implement DATs by conducting a distributional cost-effectiveness analysis [38].

### Sample size calculation

Using facility-level TB treatment outcome data from 2018 in the ASCENT facilities, overall poor treatment outcome was observed to be 17% which was higher than the overall proportion reported in Ethiopia in 2017. Since our study will also capture recurrence 6 months after the end of treatment, we have assumed the percentage with unfavourable outcome varies between 17 and 20%.

Assuming 26 facilities per arm (78 in total), a harmonic mean of 50 TB patients across facilities, a type I error of 5%, percentage with unfavourable outcome in the standard of care of 17% and 20%, the trial will have 80 and 85% power to detect a one third reduction in the unfavourable outcome with a coefficient of variation (k) of 0.35 and k ≤ 0.3, respectively. We anticipate enrolling a total of around 4000 participants from all study facilities. All adult patients diagnosed with pulmonary DS-TB will be asked to participate in our study.

### Study procedures

All patients visiting the TB clinic of the health facilities will be screened for eligibility (criteria described in the study population) by the TB care provider, and if eligible, will be offered enrolment in the ASCENT study and followed by written informed consent (see Additional file 1 for informed consent form and patient information sheet). Among those who have consented, a brief socio-demographic case report form (CRF) will be filled out with the patient by the health care provider (as trained by the study team). In addition, contact details will also be collected to implement the intervention in the two intervention arms and to facilitate follow-up 6 months after the end of treatment in all three arms (see Additional file 2 for completed SPIRIT checklist).

All participants will be treated according to Ethiopian NTP guidelines, which is a fixed dose combination of isoniazid, rifampicin, ethambutol, and pyrazinamide for the 2-month intensive treatment phase, followed by isoniazid and rifampicin for the 4-month continuation phase [28]. At treatment initiation, all participants receive basic counselling on TB by the health facility staff according to routine practice, to improve their understanding of their illness, including the need for daily medication for the full 6-month duration of their treatment. Prior to patient enrolment, staff from both intervention facilities and standard of care facility will be invited to training that will standardize the information given to participants regarding TB disease and the importance of adherence. In addition, setting-appropriate information booklets will be provided to TB participants in intervention arms and posters for health facilities in all three arms.

Participants in intervention arm 1 (smart pill box) will be given a smart box, 14 days of medication, and a DAT booklet placed inside the smart box. At each opening, the box sends a signal to ASCENT platform and a daily digital log will be kept. Participants are requested to bring the box every 2 weeks during their 1st month of treatment and monthly thereafter for refill and return the box after treatment completion, i.e., 6 months after treatment initiation. Participants in intervention arm 2 (medication label) will be provided with 14 days of medication, a medication label with a number code, and a DAT booklet. The same refill schedule is used as for intervention arm 1 (smart pill box). Participants will be asked to send the number written on the medication label via short message service (SMS) to a standard number printed on the label every day after taking their daily dose. In the intervention arms, adherence data will be collected via the DAT on the ASCENT adherence platform, and TB care providers will use these data to offer patient-centred care. Participants in the intervention arms will also be offered educational and motivational messages through SMS. In addition, TB care providers will assist the participants to resolve any problems related to the DAT, as necessary. Participants in the intervention arm who decline to participate and participants in the standard of care arm will follow the standard care for TB treatment supervision as per the NTP (Table 2).

**Table 2 Tab2:** Summary of activities in the intervention and standard of care arms

Activities	Intervention arms	Standard of Care arm
Counselling for TB adherence at treatment start	Patient education on adherence counselling will be provided as per standard of care	Patient education on adherence counselling will be provided as per standard of care
Registration and informed consent [research activity]	Adult patients satisfying the inclusion criteria and who consent to be enrolled into the study will provide written informed consent Patient will be registered on ASCENT adherence platform and upon registration receive confirmation verbally and/or by text message	Adult patients satisfying the inclusion criteria and who consent to be enrolled into the study will provide written informed consent
Data collection for the socio-demographic case report [research activity]	Tool delivered by the HCW	Tool delivered by the HCW
Explain DAT as a support tool for intervention	Delivered by HCW (standardised script) and pictorial booklet	Not applicable
TB treatment supervision	Self-administration of TB medication with support of DAT	As per standard of care (DOT at health facility or patient’ home or workplace, or self-administration)
TB medication provision	As per standard of care	As per standard of care
Daily dosing reminder	A reminder message to patient will be sent if a dose was not recorded on the platform* Depending on patient preference, the smart pill box can also remind participants using LED and/or sound	No reminder
Follow-up visits for treatment	Participants will be provided a return date to visit the health facility for refill	As per standard of care in the facility
Follow-up visit for treatment reminders	Depending on the DAT-, patient- and HCW preferences, participants can receive a reminder for follow-up visit via text message* or via smart pill box	No reminder
Adherence data	Information on adherence will be collected via the DAT and available via the ASCENT adherence platform to health HCW	As per standard of care (pill counts, patient treatment cards, etc.). Daily adherence data will only be available from those undergoing the facility-based DOT
Follow up visit during treatment	HCWs have access to the ASCENT adherence platform and will use the patient’ adherence calendar for counselling Routine sputum collection at 2, 5 and 6 months	As per standard of care in the facility Routine sputum collection at 2, 5 and 6 months
Education and motivational messages	Participants can receive periodic educational and motivational messages*	None
Telephone follow up 6 months after the end of treatment	Participants will be telephoned by research staff and a brief questionnaire conducted to ascertain if TB treatment has been restarted since the end of treatment* (among those eligible)	Participants will be telephoned by research staff and a brief questionnaire conducted to ascertain if TB treatment has been restarted since the end of treatment* (among those eligible)
Follow up visit 6 months after the end of treatment for sputum collection	Participants will be reminded of their appointment 2–3 days before the scheduled date (among those eligible). On attendance at the facility (same as the enrolment facility) sputum will be collected by the HCW for culture	Participants will be reminded of their appointment 2–3 days before the scheduled date (among those eligible). On attendance at the facility (same as the enrolment facility) sputum will be collected by the HCW for culture

*Among patients with a mobile phone

As per the Ethiopian NTP guidelines [28], sputum will be collected at the 2nd and 5th month of treatment to monitor treatment response, and at 6th month upon treatment completion to determine treatment outcome. Treatment outcome data will be abstracted from the Unit TB Register. Participants who had an end of treatment outcome of cured or completed treatment will be contacted by the study team via telephone around 6 months after treatment completion to check whether treatment for TB has been restarted. Participants who were bacteriologically confirmed pulmonary DS-TB at treatment initiation will also be invited to attend the facility to give a sputum for culture to determine their TB disease status at 6-months post treatment. Participants will be reimbursed as compensation for their time and travel expenses.

Adverse consequences of study participation include a potential risk of inadvertent disclosure of TB status by possession of DATs associated with TB treatment and receipt of SMSs relating to TB treatment. Adverse events (AEs) due to inadvertent disclosure of a participant’s TB status will be monitored across study arms. Data will be captured through both (i) participant reports to HCWs at the facility level, and (ii) researchers asking participants at the telephone interview 12 months from enrolment. AEs disclosed by participants to facility HCWs will be recorded on facility social harms register.

Participation in the study is voluntary and can be halted at any time. All participants will continue to receive routine care even if they withdraw from using the DAT or the study but will be asked if their adherence and treatment outcome data as well as their status 6 months after treatment completion can be collected.

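### Recurrence counts in the primary endpoint for everyone, but phone-less treatment successes who were not bacteriologically confirmed have no described route by which it could be found

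*Protocol article*

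**What the plan says.** The Trial outcomes section makes the primary endpoint a composite of poor end-of-treatment outcome and "treatment recurrence measured 6 months after the scheduled end of treatment". The Objectives state it for adult pulmonary drug-sensitive TB participants as a whole. The inclusion criteria are "aged 18 years or over, expecting to stay in the study area for at least 12 months, not requiring hospitalization, and providing consent"; they require neither a telephone nor bacteriological confirmation. The section on the medication-label arm expects some people to have no phone: "Participants who do not have access to a mobile phone will be given a smart pill box".

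Two routes to recurrence are described.

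- **Telephone.** Table 2 lists, in both columns, a "brief questionnaire conducted to ascertain if TB treatment has been restarted since the end of treatment* (among those eligible"). The table footnote explains the asterisk as "Among patients with a mobile phone". The text below the table says instead that participants with an outcome of cured or completed "will be contacted by the study team via telephone around 6 months after treatment completion to check whether treatment for TB has been restarted", and mentions no phone restriction.
- **Culture.** Study procedures: "Participants who were bacteriologically confirmed pulmonary DS-TB at treatment initiation will also be invited to attend the facility to give a sputum for culture". The Abstract adds that they must be able to produce sputum without induction.

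The Unit TB Register is named as the source of treatment outcome only. Contact details are collected in all three arms for the six-month follow-up (Study procedures), and locator information is held for research staff making contact at 12 months (Ethical consideration and dissemination). A footnote to Table 1 counts a treatment supporter's phone as phone access. The Table 2 footnote does not.

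**The concern.** The endpoint covers everyone, but each of its recurrence routes covers only part of the trial population. Participants with a poor end-of-treatment outcome have already met the endpoint, so the gap falls only on treatment successes. Among these, someone without a phone is outside the telephone route as Table 2 states it. If that person was also not bacteriologically confirmed, or cannot produce sputum, the culture route is closed as well.

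The analysis plan cannot repair this. It can choose how to treat a missing recurrence status, but it cannot create the measurement. Counting these participants as recurrence-free hides whatever events they have. Dropping them removes only successes and so raises the event proportion. The group is also not a random one: the Discussion itself names limited access to mobile phones as a barrier in priority populations, and the protocol plans a subgroup analysis and a distributional cost-effectiveness analysis by socio-economic status. If phone access follows socio-economic status in this trial, the depth of ascertainment would differ across those strata.

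**Working it through.** **1. The plan's own power figure.** Inputs from Sample size calculation: c = 26 facilities per arm, m = 50 (harmonic mean), type I error 5% (taken as two-sided), control proportion p0 of 17% or 20%, one-third reduction (p1 = 2p0/3), k = 0.35 or 0.30. The standard formula for an unmatched cluster trial, solved for power, is

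power = Φ{ (p0 − p1) / √[V/(c − 1)] − 1.96 }, with V = p0(1 − p0)/m + p1(1 − p1)/m + k²(p0² + p1²).

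- p0 = 17%: 81.1% at k = 0.35 and 86.4% at k = 0.30.
- p0 = 20%: 84.4% at k = 0.35 and 89.6% at k = 0.30.

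The stated 80% and 85% are reproduced within 2 points by the 17% row.

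**2. Share with no described recurrence route.** Inputs:

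- Not bacteriologically confirmed: about 40% (Addis Ababa) and 48% (Oromia) in 2018, from Baseline assessment of the clusters. In the run-in, 67% were smear confirmed, which leaves 33%. Smear is one form of confirmation, so 33% is an upper limit for that sample.
- Treatment success: 100% − 17% = 83%, from the facility data of 2018.
- Without a phone: not given in the document. **Assumed 10-25%**, and assumed independent of diagnosis and of treatment success.

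Share of all participants = unconfirmed × phone-less × success:

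| Unconfirmed | Phone-less 10% | Phone-less 25% |
|---|---|---|
| 33% | 0.33 × 0.10 × 0.83 = 2.7% | 0.33 × 0.25 × 0.83 = 6.8% |
| 48% | 0.48 × 0.10 × 0.83 = 4.0% | 0.48 × 0.25 × 0.83 = 10.0% |

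With about 4000 participants, that is roughly 110 (2.7%) to 398 (10.0%) people. Phone-less confirmed cases who cannot produce sputum would add to this; the document gives no figure for them.

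**3. Effect on the endpoint if they count as recurrence-free.** The plan lets the composite range from 17% to 20% to allow for recurrence. At its upper end, recurrence among successes is 3/83 = 3.6%. Taking 1-3.6% as an assumed range:

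- Smallest: 2.7% × 1% = 0.03 percentage points of the composite missed.
- Largest: 10.0% × 3.6% = 0.36 points missed.

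The reduction that the trial is sized to detect is 17/3 = 5.7 points at a control proportion of 17%.

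**4. Effect if they are dropped.** The effective cluster size falls from 50 to 50 × (1 − 0.027) = 48.6, or 50 × (1 − 0.100) = 45.0. At p0 = 17% and k = 0.35, the formula in step 1 gives 80.6% and 79.0%, against 81.1%. These hold p0 at 17%. Dropping successes would also raise an observed 17% to 0.17/0.973 = 17.5%, or 0.17/0.900 = 18.9%, in any arm with that share missing.

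**The case against.** The strongest reply is that one asterisk in a summary table cannot show that nobody in this group is followed up. The text beneath Table 2 says that all those cured or completed will be telephoned. Contact details are collected in every arm for this purpose, and locator information is kept for contact at 12 months. The row for the sputum visit carries no asterisk, so phone-less confirmed cases are evidently reminded somehow. Tracing procedures are also the kind of detail that an article leaves to the full protocol. This stands in part. A reader might infer that recurrence can never be found in these participants, and the document does not support that. But the text still names the telephone as the only means, and no register search, home visit or supporter's number is described for this purpose. The conflict between table and text is in the article itself, so it is more than an omitted detail.

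A reader might also infer that the gap biases the comparison between arms, because the intervention arms have months of messages and calls and so might be easier to reach. The document does not support this either. The restriction is identical in both columns of Table 2, research staff make the call in every arm, and standard care also provides for a phone call after missed appointments. Any numerical bias would depend on reach rates and a missing-data rule that the document does not state.

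Finally, the effect is small on any reasonable assumption. That is correct, and it limits the weight of the point.

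**Conclusion.** The point holds in a limited form. Table 2 and the text of Study procedures disagree on who receives the telephone check. As the procedures are written, phone-less treatment successes who were not bacteriologically confirmed, or who cannot produce sputum, have no described route to a component of the primary endpoint. The true size is unknown, because everything turns on a phone-less percentage that the document does not give. At an assumed 10-25%, about 3-10% of participants are affected. Counted as recurrence-free, they would lower the composite by about 0.03 to 0.36 points; dropped, they would cost about 2 points of power at most. This is a modest under-count or loss of data among people without phones. It is not evidence of a biased treatment comparison, and it does not threaten the trial's main conclusion on its own. It merits correction because the correction is specific and cheap.

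**What to change.** 1. Reconcile the Table 2 asterisk with the text of Study procedures: remove the restriction to participants with their own mobile phone from the row on the six-month telephone check, and allow a treatment supporter's or household number. Table 1 already recognises supporters' phones.
2. In all three arms alike, search the Unit TB Registers of the 78 study facilities for re-registration up to 12 months after treatment initiation, and count a re-registration as restarted treatment. This gives one source that depends on neither phone access nor type of diagnosis.

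The cost is a second abstraction from registers that the team already uses, and one more contact field if a supporter's or household number is not already among the contact details. Two limits remain: re-treatment outside the study facilities is still missed, and culture stays confined to confirmed cases, so the depth of ascertainment still differs by diagnosis.
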